## Abstract

**Background:**

Preimplantation genetic testing for aneuploidy (PGT-A) was demonstrated to be superior to conventional IVF in reducing the incidence of miscarriage and abnormal offspring after the first embryo transfer (ET). PGT-A requires several embryo trophectoderm cells, but its negative impacts on embryo development and long-term influence on the health conditions of conceived children have always been a concern. As an alternative, noninvasive PGT-A (niPGT-A) approaches using spent blastocyst culture medium (SBCM) achieved comparable accuracy with PGT-A in several pilot studies. The main objective of this study is to determine whether noninvasive embryo viability testing (niEVT) results in better clinical outcomes than conventional IVF after the first embryo transfer. Furthermore, we further investigated whether niEVT results in higher the live birth rate between women with advanced maternal age (AMA, > 35 years old) and young women or among patients for whom different fertilization protocols are adopted.

**Methods:**

This study will be a double-blind, multicenter, randomized controlled trial (RCT) studying patients of different ages (20–43 years) undergoing different fertilization protocols (in vitro fertilization [IVF] or intracytoplasmic sperm injection [ICSI]). We will enroll 1140 patients at eight reproductive medical centers over 24 months. Eligible patients should have at least two good-quality blastocysts (better than grade 4 CB). The primary outcome will be the live birth rate of the first embryo transfer (ET). Secondary outcomes will include the clinical pregnancy rate, ongoing pregnancy rate, miscarriage rate, cumulative live birth rate, ectopic pregnancy rate, and time to pregnancy.

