### Trial status

The first patient was enrolled on December 1, 2021. The current version of the study protocol is version 2, dated April 12, 2021. The estimated study completion date is October 2023.

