### Sample size calculation

The sample size was calculated using an online tool (Sample Size Calculator, https://clincalc.com/stats/ samplesize.aspx) based on the following estimation: an estimated 50% and 60% of patients in the control and intervention groups will achieve live births, respectively. The sample size required is 1036 patients (two-sided alpha: 5%, power: 90% [beta: 10%]). Considering an estimated loss to follow-up rate of 10%, the final sample size will be 1152 patients, with each arm comprising 576 patients.

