### Adverse events

Training for adverse event (AE) monitoring will be carried out prior to participant enrollment for the members (including the clinicians, research assistants, and nurses) who will perform the study. AE monitoring will be conducted from the start (after providing informed consent) to the end (19 months after oocyte retrieval) of the trial. Adverse events and serious adverse events (SAEs) are defined as any undesirable medical effects (moderate or serious) occurring for participants with any allocation during the study, regardless of whether they are considered to be related to the intervention or not. All SAEs will be reported immediately to the principal investigator and the Trial Management Committee and subsequently documented in detail in the patient’s medical record and niEVT database. Appropriate medical procedures will be taken until the patients recover or are in a stable condition.

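### The abstract's target of 1140 conflicts with the body's 1152, and 24 months of enrolment from December 2021 runs past the stated October 2023 completion, leaving no time for the last births

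*Protocol article*

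**What the plan says.** **Target.** The abstract's methods paragraph states: "We will enroll 1140 patients at eight reproductive medical centers over 24 months". The Sample size calculation section assumes that "an estimated 50% and 60% of patients in the control and intervention groups will achieve live births", derives 1036 patients for 90% power at two-sided 5%, allows for 10% loss to follow-up, and concludes that "the final sample size will be 1152 patients, with each arm comprising 576 patients". Data collection and management and Statistical analyses both repeat 1152, with 576 per group.

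**Calendar.** Trial status gives the start ("The first patient was enrolled on December 1, 2021") and the end ("The estimated study completion date is October 2023"). The primary outcome is live birth after the first transfer, counted from 28 completed weeks of gestation. The Adverse events section says monitoring runs "from the start (after providing informed consent) to the end (19 months after oocyte retrieval) of the trial".

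**The concern.** These are current statements of the same quantities, and they disagree. Two recruitment targets leave it unclear where enrolment stops, and the smaller one appears in the part of the article that is read most.

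The date conflict is the more serious. The accrual period alone is longer than the interval from first enrolment to completion, before any allowance for pregnancy. The primary outcome matures slowly and unevenly: a failed transfer is known early, a live birth only many months later. If the stated completion date governed the analysis, many late-enrolled women would have no outcome, and the women with outcomes would be enriched for failures.

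**Working it through.** **1. The plan's own sample size.** Inputs from Sample size calculation: 50% versus 60%, two-sided alpha 5%, power 90%; 1:1 allocation from Randomization and masking. Pooled-variance formula, no continuity correction:

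n per arm = [1.960 × √(2 × 0.55 × 0.45) + 1.2816 × √(0.50 × 0.50 + 0.60 × 0.40)]² / 0.10² = (1.379 + 0.897)² / 0.01 ≈ 518.

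Twice 518 is 1036, the stated figure. Strict rounding up gives 519 per arm (1038), a trivial difference.

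**2. Where the two targets come from.**

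| Inflation for 10% loss | Result | Left after 10% loss | Power |
|---|---|---|---|
| 1036 / 0.90 = 1151.1 | 1152 (576 per arm) | 1036.8 | 90.0% |
| 1036 × 1.10 = 1139.6 | 1140 | 1026 | 89.7% |

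Dividing by 0.90 is the form that keeps 1036 after the loss. The abstract's 1140 matches the multiplication form and falls 10 short. The cost is 0.3 percentage points of power.

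**3. The calendar, forwards.**
- 1 December 2021 to 31 October 2023 is 23 months, shorter than the 24 months of enrolment.
- 24 months of enrolment ends about 30 November 2023.
- Taking a blastocyst at transfer as 2 weeks 5 days of gestation (assumption), 28 weeks is reached 25.3 weeks (5.8 months) later and 40 weeks is reached 37.3 weeks (8.6 months) later. With no gap between enrolment and transfer, the last primary outcomes fall between late May and mid-August 2024.
- Adding 19 months to the end of enrolment gives about the end of June 2025. The 19 months count from oocyte retrieval and the article gives no enrolment-to-retrieval interval, so this is approximate: about mid-2025 or later.

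**4. The calendar, backwards.** For October 2023 to be the true end:
- with 19 months after retrieval, the last retrieval is about the end of March 2022. That means 1152 women in about 4 months, 1152 / 4 = 288 per month;
- with term birth after the first transfer only, accrual ends about mid-February 2023 (23.0 − 8.6 = 14.4 months), so 1152 / 14.4 = 80 per month.

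The abstract implies 1152 / 24 = 48 per month.

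**5. Size of the gap if data were cut on 31 October 2023.** Assumptions, none given in the article: even accrual of 48 per month, failures known 3 months after enrolment, births 9 to 12 months after enrolment. The overall live birth rate of 55% is the mean of the plan's 50% and 60%.
- Known failures: 0.45 × 48 × (23 − 3) = 0.45 × 960 = 432.
- Known births: 0.55 × 48 × (23 − 12) = 0.55 × 528 = 290, up to 0.55 × 48 × (23 − 9) = 0.55 × 672 = 370.
- Known outcomes: 722 to 802 of 1152, or 63% to 70%. So 30% to 37% are unknown, including the 48 women not yet enrolled.
- Live birth rate among known outcomes: 290 / 722 = 40% to 370 / 802 = 46%, against 55% assumed.

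**6. Effect on the comparison, same assumptions (24 per arm per month).** At a 12-month lag, control is 132 / (132 + 240) = 35.5% and intervention 158.4 / (158.4 + 192) = 45.2%. At 9 months they are 168 / (168 + 240) = 41.2% and 201.6 / (201.6 + 192) = 51.2%. The difference is 9.7 to 10.0 points against the planned 10. With equal timing in both arms, the rates are pulled down but the difference barely moves.

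**The case against.** **The target mismatch is a slip in the abstract.** This stands. Three sections of the body give 1152, that number delivers 90% power, and nothing says that recruitment stops at 1140. A reader might infer that the trial is underpowered; the documents do not support that. Even 1140 gives 89.7%, and choosing unpooled variance (about 515 per arm, 1030 in total) moves the requirement by nearly as much.

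**October 2023 is an estimate under Trial status, not an analysis cutoff.** This also stands. No section makes it a database lock, and the Statistical analyses section plans on 1152 patients. An optimistic date may simply slip. The missing outcomes in step 5 are therefore conditional on a cut at that date. The contradiction between the dates is not.

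**A reader might infer that about half the women would have no primary outcome.** Applying the 9–12 month birth lag to everyone does give only 528–672 of 1152 (46–58%) with outcomes. But women whose first transfer fails have a known outcome much earlier, so the supported range is 30–37% unknown.

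**The 19 months is the adverse-event window, not the primary-outcome window.** Correct as to the primary outcome, which is why step 5 does not use it. The same sentence, however, equates that point with the end of the trial, so it does bear on the completion date.

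**Other readings do not remove the conflict.** If 24 months were total duration, it would still end about a month after October 2023, and the text says that patients are enrolled over that time. If October 2023 meant the end of recruitment, it would still fall short of 24 months, and the text refers to study completion.

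**Conclusion.** Both contradictions hold on the face of the document and need no outside source.

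- **Target:** 1140 is wrong against the plan's own inputs, by 12 enrolled patients and 10 evaluable ones, at 0.3 points of power. This is minor and editorial.
- **Calendar:** the completion date falls about a month before enrolment would end, about 7 to 10 months before the last first-transfer births at 28 to 40 weeks (with no enrolment-to-transfer gap), and about 20 months before the stated end of the trial. This is the part with weight.

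The estimate of 30–37% unknown outcomes rests on even accrual, the assumed lags and a data cut that the article does not state. It shows why the date needs correcting; it does not predict what the investigators will do. It would be going too far to say that the planned primary data will not be delivered, or that the treatment difference would be materially biased: under equal timing in both arms it would not be. If failures become known at different times in the two arms, that last reassurance no longer applies.

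**What to change.** 1. Replace 1140 with 1152 in the abstract.
2. Reconcile the accrual period, the completion date and the follow-up. If 24 months of accrual stands, date completion as the last oocyte retrieval plus 19 months, about mid-2025 or later. If October 2023 is the firm date, the accrual period and monthly rate must be restated to fit it (step 4 shows what that would require).
3. State that the primary analysis will not take place before the last first-transfer pregnancies have had time to reach birth. This need not wait for women lost to follow-up, whom the plan already expects at 10%.

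The cost is a text correction and a later, realistic completion date. Design, sample size and analysis method are unchanged.

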**Discussion:**

In this study, patients who undergo noninvasive embryo viability testing (niEVT) will be compared to women treated by conventional IVF. We will determine the effects on the pregnancy rate, miscarriage rate, and live birth rate and adverse events. We will also investigate whether there is any difference in clinical outcomes among patients with different ages and fertilization protocols (IVF/ICSI). This trial will provide clinical evidence of the effect of noninvasive embryo viability testing on the clinical outcomes of the first embryo transfer.

**Trial registration:**

Chinese Clinical Trial Registry (ChiCTR) Identifier: ChiCTR2100051408. 9 September 2021.

## Background

Preimplantation genetic testing for aneuploidy (PGT-A) was demonstrated to lead to better clinical outcomes than conventional IVF (based on morphological assessment) in several clinical studies [1–3]. PGT-A can precisely detect embryonic chromosome abnormalities, effectively reduce pregnancy loss, and promote healthy live births in patients undergoing IVF cycles. For a long time, PGT-A was performed using samples taken from embryos in different developmental stages (cleavage stage, blastocyst stage) [4]. Trophectoderm biopsy (TE biopsy) is the most widely applied biopsy method compared to polar body and cleavage-stage biopsies in clinical practice. Some studies have claimed that TE biopsy does not affect embryo development potential [5, 6]. However, other works have reached the opposite conclusion [7, 8]. Despite contradictory opinions, trophectoderm biopsy (TE biopsy)-based PGT-A has been widely applied in IVF cycles worldwide. However, invasive biopsies may negatively affect embryo development, and their effect on the long-term health of offspring is unclear. In addition, embryo biopsy increases the financial burden on patients because it relies on professional equipment and skilled embryologists [9]. For these reasons, doctors and patients are eager for a noninvasive PGT-A (niPGT-A) protocol.

The identification of embryonic DNA in the blastocoel fluid (BF) and spent blastocyst culture medium (SBCM) provides an opportunity to determine the embryo chromosomal status in a noninvasive way [10, 11]. Because of advantages such as the existence of a larger volume of embryonic DNA, easier sample retrieval, and avoidance of any embryo manipulation, SBCM is more widely used in niPGT-A than BF. Since the publication of the first proof-of-concept study demonstrating the potential of niPGT-A in 2016 (Shamonki et al., 2016), several works have briefly compared the performance of niPGT-A (using SBCM) and PGT-A (using TE biopsy, the inner cell mass, and the whole blastocyst) [12–14]. These studies reached a general conclusion that niPGT-A has a comparable accuracy to PGT-A. Despite the obvious advantages of niPGT-A over PGT-A, the clinical benefit of niPGT-A needs to be further evaluated in strictly designed randomized controlled trials (RCTs) with large samples.

To our knowledge, there are three (two prospective studies and one retrospective study) studies reporting clinical assessments of niPGT-A in different patients [15–17]. Chen et al. developed a machine learning algorithm that was used for embryo grading based on niPGT-A results. The algorithm was validated to be effective in avoiding wastage of potentially competent embryos in a cohort of 266 patients (aged 20 ~ 45 years). Fang et al. reported the transfer of 52 embryos determined to be euploid by niPGT-A in 43 patients (aged 23 ~ 42 years) with or without chromosomal rearrangements. Xi et al. conducted a retrospective study that demonstrated that niPGT-A effectively improved the clinical outcomes in patients with both recurrent pregnancy loss (173 patients) and repeated implantation failure (100 patients) compared to conventional IVF. Although these studies provide preliminary insights into the clinical benefits of niPGT-A, they suffer from a series of limitations, including limited study centers (all three studies were conducted in a single clinical center), a lack of proper control, and relatively small sample sizes. Consequently, a double-blind, multicenter RCT with a large sample is required to achieve a solid conclusion regarding the clinical benefits of niPGT-A.

The aim of this study is to evaluate whether noninvasive embryo viability testing (niEVT) results in better clinical outcomes than conventional IVF. niEVT assesses embryo developmental potential by integrating niPGT-A results (priority standard) with morphological grading results (second standard). Conventional IVF predicts embryo developmental potential based only on morphological grading results. In addition, we will also investigate which subgroup of patients is more likely to benefit from niEVT by comparing the clinical outcomes of patients with different ages and fertilization protocols.

### Trial objectives

PGT-A was demonstrated to be a reliable method for detecting aneuploid embryos during IVF. Polar body, cleavage-stage, or trophectoderm biopsies are required to obtain samples from embryos. This invasive sampling process raises concerns regarding the possible negative impact on clinical outcomes. Noninvasive preimplantation genetic testing for aneuploidy (niPGT-A), which detects chromosomal abnormalities in the cell-free DNA (cfDNA) of spent blastocyst culture medium, is expected to be applied in clinical practice. However, it is not clear whether niPGT-A can achieve better clinical outcomes than conventional IVF. In this study, patients who undergo noninvasive embryo viability testing (niEVT) will be compared to women treated by conventional IVF. We will determine the effects on the pregnancy rate, miscarriage rate, and live birth rate and adverse events. We will also investigate whether there are any differences in the clinical outcomes among patients with different ages and fertilization protocols (IVF/ICSI).

## Methods

### Trial design

This protocol is for a multicenter, double-blinded, randomized, controlled trial that will be conducted in China (Fig. 1). This protocol was revised several times by experts to form this final version before trial commencement. Patient recruiting is being carried out simultaneously in eight reproductive medical centers, including the First Medical Center of PLA General Hospital (PLAGH), the Sixth Medical Center of PLA General Hospital (6MC-PLAGH), the Air Force Medical University-Tangdu Hospital (Tangdu Hospital), the 900th Hospital of the Joint Logistics Team (900 Hospital), the Third Affiliated Hospital of Sun Yat-Sen University (3AH-SYSU), Henan Provence People’s Hospital (Henan-PPH), the University of Hong Kong-Shenzhen Hospital (HongKong-SH), and the Zhuhai Center for Maternal and Child Health Care (Zhuhai-CMCHC). Three rounds of clinical inspections will be conducted in every reproductive medical center by a trial management committee (TMC). The aim of the clinical inspections will be to ensure that the study is performed according to the protocol and that the data are collected and recorded in a timely manner.

### CONSORT statement

The reporting checklist for this protocol is based on the CONSORT guidelines [18].

### Trial status

The first patient was enrolled on December 1, 2021. The current version of the study protocol is version 2, dated April 12, 2021. The estimated study completion date is October 2023.

**Fig. 1 Fig1:**
[figure not shown]
CONSORT flow diagram showing the procedure of this randomized controlled trial. Abbreviations: niEVT, noninvasive embryo viability testing; niPGT, noninvasive preimplantation genetic testing

### Study participants

Eligible subjects must meet all the inclusion criteria. To be enrolled, the following criteria must be met: (1) Couples experiencing infertility who are undergoing their first IVF cycle; (2) Couples undergoing IVF or ICSI as the fertilization protocol; (3) Couples in which the female is aged 20–43 years; (4) Couples in which the female has a body mass index (BMI) of 18–25 kg/m^2^; (5) Couples who agree to the performance of single culture of all embryos on Day 4 (after fertilization); (6) Couples with ≥ 2 good-quality (morphological grade superior to 4 CB) blastocysts on Day 5/6 after fertilization; (7) Couples who agree to undergo single frozen-thawed blastocyst transfer; and (8) Couples in which both partners provide written informed consent.

Subjects who met any of the exclusion criteria will be excluded from the study. The exclusion criteria are as follows: (1) Couples (with any contraindications) who are unable to undergo in vitro fertilization; (2) Couples (with a known chromosomal abnormality) who are eligible for preimplantation genetic testing (PGT) cycles; (3) Couples in which the female has unexplained recurrent miscarriage (≥ 2 times); (4) Couples in which the female has diseases that affect the pregnancy outcome (e.g., untreated hydrosalpinx, untreated intrauterine infection, uterine fibroid diameter > 4 cm, pelvic and abdominal benign tumors > 4 cm, hCG daily endometrial thickness < 7 mm, pituitary tumors and malignant tumors of various tissues and organs); (5) Couples in which the female has a congenital uterine anomaly (e.g., septate uterus, bicornuate uterus, unicornous uterus) or an acquired intrauterine pathology (e.g., adenomyosis, submucosal leiomyomas, intrauterine adhesions); and (6) Couples with severe male factor infertility (e.g., aspermia, azoospermia, cryptozoospermia).

### Recruitment

Potential participants will be screened from the regular infertile outpatients during their first visit at the reproductive medical center. Eligible patients complying with all inclusion criteria will be invited to receive a free consultation with the doctors or clinical research assistants to discuss the study procedure and all possible outcomes of the trial. Patients who agree to enroll must sign a written informed consent form before any procedures can be carried out. The participants have the right to withdraw their consent and quit the trial at any time for any reason, without any consequences.

### Randomization and masking

Randomization and allocation will be controlled centrally by a web-based niEVT administration database. The randomization will be stratified by fertilization protocol (IVF, ICSI) and by age (< 35, ≥ 35 years). Eligible patients will be independently allocated to either the intervention group (niEVT) or control group (morphological assessment) in a 1:1 ratio using a dynamical stratified blocked randomization algorithm with a block of 6. Regarding patient allocations, the embryologist, research assistants, clinicians, and patients will be blinded.

### Interventions

Oocyte retrieval and fertilization (either IVF or ICSI) will be performed according to the standard protocols of each reproductive medical center. For every eligible patient, all embryos will be cocultured in the same medium drop for the first three days after fertilization (Day 0). On Day 4, embryos will be separately washed 3 ~ 5 times to maximally remove potential maternal/paternal DNA contamination derived from polar cells, cumulus cells, and sperm and then cultured individually to Days 5/6. Morphological grading will be performed on Day 5/6 to determine whether a good-quality (superior to grade 4CB) blastocyst has developed according to Gardner’s criteria [19]. After that, the embryos will be vitrified, and the spent blastocyst culture medium will be collected.

For patients in the intervention (niEVT) group, the embryo transfer order will be determined based on the niPGT-A results (primary standard) and morphological grading results (secondary standard). The embryos will be ranked into three groups: Class 1, with a chromosome status of euploid; Class 2, with an undetermined chromosome status (failed genetic testing or noninformative results); and Class 3, with a chromosome status of aneuploid. Embryos of the same group will be further ranked according to their morphological grades (5AA > 5AB > 5BA > 4AA > 4AB > 4BA > 6AA > 6AB > 6BA > 5BB > 4BB > 6BB > 5AC > 5BC > 4AC > 4BC > 6AC > 6BC > 5CA > 5CB > 4CA > 4CB). Embryos in the same group and with the same morphological grade will be randomly selected for transfer. Based on the rules described above, the embryo transfer order can be achieved. A clinical report with the patient information, embryo IDs, and embryo transfer order will be generated and sent to the clinician. Neither the niPGT-A results nor the morphological grading results will be shown on the report.

For patients in the control (conventional IVF) group, the embryo transfer order will be determined based only on the morphological grading results. A similar clinical report in the same format will be generated and sent to the clinician. The morphological grading results will not be shown on the report.

For patients in both groups, the clinicians will perform a single frozen-thawed blastocyst transfer [20] up to three times according to the embryo transfer order of the clinical report. If the prior embryo transfer fails (no conception for any reason), a second/third embryo transfer will be performed.

